### Eligibility criteria, registration and consent

#### Cluster level

Participation was solicited from organizations via invitation letters to their respective managers that enclosed study information and a reply form with an individualized link for online reply. Inclusion criteria at cluster level were (1) organization with an on-site, meal producing staff canteen; (2) location in the canton of Bern, Solothurn, Aargau, Basel-Stadt, Basel-Land, Zurich, Zug, or Luzern; (2) at least 50 employees (exclusive of catering staff); and (3) the canteen sells at least 50 luncheons per day. All queried organizations that met these requirements, or that did not, as well as those refusing participation were asked if health promotion is part of the corporate mission in order to evaluate whether this influenced willingness or interest in participation. Indication of reason for refusal was optional. Interested organizations indicated general characteristics including kind of catering operation, number of employees, whether it was a shift operation, and whether it would accept random allocation to the intervention or control arm. After an on-site meeting with the investigator, organization and catering operation managers communicated their final decision for participation in the intervention or control arm. A gatekeeper agreement governed the rights, commitments, and cooperation between the organization, if applicable the catering firm, and the university. A study coordinator was designated at the organizational level, usually the person responsible for workplace health promotion.

#### Participant level

Operation management informed employees about study participation via email, intranet, and/or bulletin board and invited them to an on-site information session with the research group. A brief outline of the study included in the message listed the inclusion criteria: (1) men, and women who are not pregnant; (2) employment at the organization for at least one year from the beginning of the intervention in any job in the organization except a position in the staff canteen; (3) age 15–65 years; (4) eating on average twice a week or more in the staff canteen; (5) proficiency in German; (6) no kidney or cardiovascular disease, or medication intake or any other issue affecting urine collection or analysis; (7) no severe food intolerance or allergy that prevents food intake in the staff canteen. Attendees of the intervention sessions were given study information that included the consent form in duplicate, and a reply form with secure link for online registration. The same documents were disseminated to employees who did not attend. Within two weeks, employees registered using the reply form giving their name, age, professional position, contact information, etc., and also giving written, signed consent (if younger than 18 years, also by legal representative).

As permitted by the organizations, we conducted an additional, anonymous online nonresponder survey. It was combined with the study health questionnaire (see below) and assessed reasons for nonparticipation [43]. Results will be reported elsewhere.

### Study objectives

The primary objective was to demonstrate the effectiveness of a combined educational and environmental intervention in the workplace and staff canteen in reducing consumers’ mean daily total dietary NaCl intake by at least 15% in comparison to consumers served regular luncheons and having access only to general, publicly available information on healthy eating. Following the key health promotion approach of empowerment [44, 45] at organisational and individual levels, the secondary objectives were to improve the generic and nutrition-specific health literacy (HL) [46, 47] of employees and enhance guideline compliance among the catering facility team.

The study further pursued an exploratory objective: to validate both a Na- and K-specific food record checklist and a late afternoon spot-urine measurement against 24-h urinary excretion.

### Primary outcome measure

Changes in Na/NaCl intake (estimated from 24-h urinary Na excretion) in the intervention as compared with the control group.

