## Background

Stroke and ischaemic heart disease are the most common noncommunicable diseases and causes of disability and death worldwide [1, 2]. These cardiovascular diseases (CVD) impose a large economic burden: in Switzerland the annual direct health care costs attributable to CVD were estimated to be CHF 10.3 billion in 2011 [3].

About half of CVD events are estimated to be attributable to high blood pressure [4]. Yet many people are unaware of being hypertensive [5, 6], and strokes and ischaemic events often occur without prior diagnosis of hypertension [7]. Population-wide governmental strategies aim to lower dietary and other lifestyle risk factors for hypertension/CVD and promote protective factors [8, 9]. Experts acknowledge the health protective, blood pressure reducing role of a restricted sodium (Na) intake below an average of 2 g (87 mmol) per day [10, 11]. In addition, a sufficient potassium (K) intake (> 3.5 g (90 mmol)/day) and a dietary Na/K ratio below 0.6 by weight (< 1 by mmol) is a related public health goal [12]. Countries worldwide have established national programs for stepwise shifting of the overall population Na intake distribution [13] towards 30% lower intakes [14, 15].

Based on research on population Na intake [16, 17] and Na content of foods/catering offerings [18–20], the Swiss salt strategy defined an intermediate goal for Na intake reduction of at least 16% for the population in four years. That is, from an average of 3.5 g to below 3 g Na, or from 9 g to less than 8 g salt equivalent (short salt, NaCl) intake per day [21] -the final long-term target being 5 g/day [10]. The food industry, excepting food service (catering), became involved in a voluntary reformulation program [22] to reach defined Na goals (e.g., [23]). However, actions targeting eating behavior to reduce Na intake have not been pursued in the absence of consistent evidence of their effectiveness [24]. The national research program NRP69 Healthy Nutrition and Sustainable Food Production, which was seeking practical answers to how people in Switzerland can achieve a healthy diet, offered a framework to investigate feasible ways of Na intake reduction [25].

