### Study design

Healthful & Tasty is a combined educational and environmental trial in the Swiss workplace to promote health by lowering Na intake in a nutritionally balanced, healthy diet. Health promotion activities in the workplace are typically driven by legal responsibilities for occupational health and safety in Switzerland. Nutrition education and structural measures in catering facilities are not standard components in the national program Friendly Work Space [35]. Moreover, many organizations with staff canteens outsource catering and related food health responsibility to large catering firms, which offer labeled, nutritious menus. The trial recruited organizations and their employees, but catering firms had to agree to the intervention as well. We established a cluster randomized controlled trial (cRCT), received ethical approval by Swissethics, and registered the trial in September 2014.

Considering experiences from our own studies in communal catering [18, 19, 36, 37] and reports in the literature [38–41], and in agreement with the NRP69 scientific steering committee we prepared for having to adjust the study design if recruitment with randomization and matching at cluster level proved to be infeasible within six months (Table 1).

**Table 1 Tab1:** Study design options of the “Healthful & Tasty: Sure!” workplace trial

	Experimental study design	Alternative quasi-experimental study design
Design	Cluster randomized controlled trial	Cluster nonrandomized single arm trial with calibration arm
Blinding	No	No
Pair-wise matching	Yes	No
Sample size estimation (power calculation)	Assumptions: baseline mean 24-h urine sodium excretion of 180 mmol [16, 17, 42], standard deviation of 65, intra-cluster correlation coefficient of 0.05, 16 clusters and drop-out rate of 25%. Objective: detect between-group difference of at least 15% (i.e. 27 mmol) at trial end with alpha 0.05 and 80% power.	Assumptions: baseline mean 24-h urine sodium excretion of 180 mmol [16, 17, 42], standard deviation of 65, intra-cluster correlation coefficient of 0.05, and drop-out rate of 10%. Objective: detect sodium intake reduction by 15% (i.e. 27 mmol) until trial end with alpha 0.05 and 80% power.

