### Statistical analysis

For baseline analysis, continuous variables were summarized descriptively using mean and 95% confidence interval (CI) or median and range depending on sample size and type of variable. For categorical variables, we used frequency and percentage. Variables were summarized overall, separately for intervention and control group, and by sex. At cluster level, Na, K, and NaCl levels of menu components were calculated weighted for sales numbers. At participant level, comparisons between groups were performed using t-tests for continuous variables, and chi-squared tests or Fisher’s exact tests for categorical variables depending on the expected number per cell. We applied two-tailed tests with significance level 0.05 for all analyses. Because baseline analysis was exploratory and hypothesis generating, no adjustment for multiple testing was done.

We used and will use baseline data to explore factors related to salt intake and evaluation of questionnaires. Statistical analyses are described in the respective articles [71, 91]. Future analysis will include application of a linear mixed model with organization as random effect to assess the change in primary outcome from t0 to t12. All analyses are run using R 3.3.2 [92].

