#### Cluster level

A total of 389 organizations with catering facilities were assessed for eligibility. Of these, 146 were not reached, 186 declined to participate, and 49 did not meet the inclusion criteria. Finally, eight organizations were included in the trial, seven participating in the intervention arm and one in the control arm.

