Our experience showed that implementing intervention trials in the workplace is highly sensitive to how the real-world setting meets scientific demands [100, 101]. We chose a cRCT, which is commonly viewed as the most reliable design to assess the effectiveness of interventions and avoid bias [102]. However, the enrollment rate of organizations in our trial was much lower than expected, and interested organizations did not accept being randomized to intervention or control arms, which confirms observations made by Kwak et al. [39] who recognized randomization as one of the most important reasons why organizations refuse to participate in trials. For these reasons, and time constraints, we adjusted to a quasi-experimental study design. The final, cluster nonrandomized single-arm trial with calibration arm still allows following all participants and estimating intervention effectiveness with sufficient robustness [41, 103]. Participation at individual level was modest, but we anticipated a high follow-up rate since most participants seemed committed to participating in education workshops during the workday, and receiving regular measurement results of blood pressure, weight, Na and K intake, etc., as well as coupons for eating in the staff restaurant as compensation at study end.

We will use the RE-AIM (reach, effectiveness, adoption, implementation, and maintenance) framework [104] to estimate the trial’s final overall impact. Finally, we recognize that study findings can only be applied to similar organizations, not to the overall working population in Switzerland, since only certain German-speaking cantons were included and sample size was small.

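### The primary objective and outcome are worded against a control arm of one organization with 13 people, while the stated 80% power and the planned model concern a change within the intervention arm

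*Protocol article*

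**What the plan says.** Between-arm statements in the protocol article:

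- Study objectives: the primary objective is a reduction of at least 15% in mean daily salt intake "in comparison to consumers served regular luncheons and having access only to general, publicly available information on healthy eating".
- Primary outcome measure: "Changes in Na/NaCl intake (estimated from 24-h urinary Na excretion) in the intervention as compared with the control group". The secondary and canteen outcomes are worded against control in the same way.

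Within-arm statements in the same article:

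- Study design, Table 1, final design: "Cluster nonrandomized single arm trial with calibration arm", with "Objective: detect sodium intake reduction by 15% (i.e. 27 mmol) until trial end with alpha 0.05 and 80% power". The number required is given for intervention clusters only: seven clusters, N = 112.
- Recruitment: cluster recruitment ended for lack of time, once that intervention-arm minimum had been met.
- Statistical analysis: a linear mixed model with organization as random effect is planned "to assess the change in primary outcome from t0 to t12". The sentence names no arm contrast.

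What was achieved: of eight organizations, "seven participating in the intervention arm and one in the control arm". At baseline 128 intervention and 13 control participants had adequate 24-h urine samples. Under Strength and limitations, the final design "still allows following all participants and estimating intervention effectiveness with sufficient robustness".

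**The concern.** The superseded cluster randomized design powered a between-group difference. The final design dropped that contrast from the sample size, but the objective and outcome sections still carry it. A reader cannot tell which result is primary, and will naturally attach the 80% power to the comparison named as the primary outcome.

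Both ways of proceeding cause trouble. If the between-arm comparison is run as worded, it is badly underpowered, and it looks falsely precise if clustering is ignored. If the within-arm change is reported in its place, the objective's comparison with people served regular luncheons has no support. With one control organization, anything peculiar to that organization over the year is indistinguishable from the absence of the intervention. Its deviation can be judged only by borrowing the between-organization variance of the seven intervention organizations.

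**Working it through.** **Inputs.** From Table 1, final design: baseline mean 180 mmol, target 27 mmol (15%), SD 65, ICC 0.05, drop-out 10%, 7 clusters, N = 112. From the Participation section: 128 and 13 participants, 7 and 1 organizations. Two-sided 0.05 is taken from the Statistical analysis section.

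**Step 1: which comparison does the 80% fit?** One-sample test of a mean change, with n = 7m participants: SE = 65 × √[(1 + (m − 1) × 0.05)/n], noncentral t with 6 df.

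- m = 16, n = 112: SE = 65 × √(1.75/112) = 8.125; 27/8.125 = 3.32; power 79.0%.
- After 10% drop-out, m = 14.4, n = 100.8: SE = 65 × √(1.67/100.8) = 8.37; 27/8.37 = 3.23; power 76.7%.
- The normal approximation gives 91.4% and 89.7%.

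The same cluster-t approach recovers the superseded design. With 8 clusters per arm and 395 less 25% = 296 per arm, SE = 65 × √(2 × 2.8/296) = 8.94, and with 14 df power is 80.2%. So the 80% in the final design fits a within-arm change, most closely if 112 is the number analysed. The table labels 112 as the number before drop-out.

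**Step 2: power of the primary outcome as worded.** After 10% drop-out, 115.2 and 11.7 participants are analysed. For now, 65 is treated as the SD of the change.

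- Intervention: mean cluster size 115.2/7 = 16.46; design effect 1 + 15.46 × 0.05 = 1.773; variance 4225 × 1.773/115.2 = 65.0.
- Control: design effect 1 + 10.7 × 0.05 = 1.535; variance 4225 × 1.535/11.7 = 554.3.
- SE = √(65.0 + 554.3) = 24.9 mmol; 27/24.9 = 1.085.
- Power: 19% (normal) or 15% (t, 6 df). Without drop-out: 20% or 16%.
- 95% half-width: 1.96 × 24.9 = 49 mmol, or 2.447 × 24.9 = 61 mmol.
- Detectable with 80% power (normal): 2.80 × 24.9 ≈ 70 mmol, which is 39% of 180.

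The control organization supplies 554.3/619.3, about 90%, of the variance.

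**Step 3: the SD assumption.** Table 1 does not say whether 65 is the SD of one measurement or of a change. If it is one measurement, the change SD is 65 × √[2(1 − r)], with r the t0–t12 correlation. The article gives no r, so the values below are assumptions (ICC 0.05, 10% drop-out):

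| r | SD of change | SE | Power, t (6 df) | Power, normal |
|---|---|---|---|---|
| 0.3 | 76.9 | 29.5 | 12% | 15% |
| 0.5 | 65.0 | 24.9 | 15% | 19% |
| 0.7 | 50.3 | 19.3 | 22% | 29% |
| 0.8 | 41.1 | 15.7 | 30% | 40% |

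**Step 4: other scenarios.**

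- No clustering at all, SD of change 65: about 27% after drop-out.
- No clustering and r = 0.8: about 57% after drop-out and 62% without drop-out (normal), the most favourable case run.
- Unlimited participants in the single control organization, SD 65, ICC 0.05, 128 intervention participants: SE 16.5 mmol, power 28–37%. More control participants would not solve the problem of having one control cluster.

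**The case against.** The strongest reply is that no passage plans the test computed in Step 2. The planned model concerns change over time. The Abstract, Background and Discussion give the 15% aim without a comparator, and the single-arm label points to the within-arm change as the working target. On this view the objective and outcome sections simply kept wording from the randomized design. That is probably how it arose, and it makes this a failure to reconcile text. It is still a defect, because the retained wording sits in the sections that define what is primary.

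The limits are also partly disclosed. The article mentions small cluster and participant numbers, the failure to randomize and restricted generalizability, and says the ethics committee approved the change and the registration was annotated. This stands. However, no power is given for the comparison as worded, and the claim that the design "still allows following all participants and estimating intervention effectiveness with sufficient robustness" goes further than those caveats allow.

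Two stronger readings are not supported:

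- A reader might infer that the between-arm result is almost certain to be inconclusive. The power depends on a correlation the article does not give and on applying ICC 0.05 to change. Underpowered is supported; near-certain failure is not.
- A reader might infer that a national salt programme accounts for a calculable part of any decline, since the Swiss strategy "defined an intermediate goal for Na intake reduction of at least 16% for the population in four years". The article does not date that goal or the reformulation programme, states a target and not an observed trend, and excludes catering from the reformulation. It supports no yearly figure to subtract.

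**Conclusion.** The contradiction holds. The objective and outcomes are between-arm; the sample size, stated power and planned model are within-arm. On Table 1's SD and ICC with 10% drop-out, the comparison as worded has about 15–19% power for 27 mmol if 65 is the SD of change, and about 12–40% if it is a single-measurement SD with r between 0.3 and 0.8. No scenario run reaches 80%. All these figures borrow the between-organization variance from the intervention arm, because one control organization supplies none of its own.

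The within-arm figure is close to what is claimed: about 79% with 112 analysed and about 77% after the table's 10% drop-out (t, 6 df). It rests on the same SD question; at r = 0.3 it would be 65% and 63%. The description of the effectiveness estimate as sufficiently robust is not supported for a comparative effect.

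**What to change.** 1. Restate the primary objective and primary outcome as the t0–t12 change in 24-h urinary sodium within the seven intervention organizations.
2. Attach the stated power to that quantity only. Note that it is about 79% with 112 analysed and about 77% after 10% drop-out (t, 6 df), and say whether 65 is the SD of a change or of one measurement.
3. Report the control organization's change descriptively with its confidence interval, as calibration, without a confirmatory between-arm test. Align the wording of the secondary and canteen outcomes.
4. Under Strength and limitations, replace the robustness claim with a statement that the result is an essentially uncontrolled before–after change.

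Keeping the between-arm outcome and stating its low power would also remove the contradiction, but would leave as primary a comparison the design cannot deliver. The recommended change needs revised wording and a registry annotation, and no new data; the article describes the primary analysis as still to come. The cost is a less favourable claim: a change over time, not an effect against usual catering.

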### Secondary outcome measures

Changes in the overall qualitative diet composition (Na/K ratio), blood pressure, anthropometric indices, generic HL, and nutrition-specific HL in the intervention as compared with the control group. In addition, iodine (I) intake was monitored because table salt is fortified with iodine to ensure sufficient population intake in Switzerland [48].

Changes in Na/NaCl and K levels in luncheons offered daily and consumed regularly in the intervention catering facilities as compared with their levels in the control organisations’ catering facilities.

### Intervention design

The staggered, four-phase (4 × 3 months) community trial over the course of one year in organizations with staff canteens combined educational and environmental interventions with regular follow-up measures in the intervention arm, compared to measures in organizations without intervention (control arm). Both the educational and environmental intervention programs covered five themes, implemented in four to five events, and included evaluation steps. They were matched with a maximum five follow-up measurements per person and canteen, at start/baseline (t0), after three (t3), six (t6), nine (t9), and 12 months (t12, end) (Fig. 1).

**Fig. 1 Fig1:**
[figure not shown]
Flow diagram of intervention trial elements, baseline to study end

### Environmental intervention, theoretical background and program

With a view to develop and strengthen individual and environmental resources, the catering intervention aimed at creating a supportive nutrition environment for health in the workplace [49–51]. The coaching of catering teams was based on the awareness-to-adherence model [52] applied in the context of health risk management and it should enhance guideline compliance [53, 54]. The Hazard Analysis and Critical Control Points (HACCP) concept served as a model to control critical points of salt entry in luncheon production [18]. We hypothesized that becoming more knowledgeable and aware about food health risks and means of their practical management will empower catering staff to adopt the Swiss quality standards for health-promoting communal catering (SQSCC) [55]. We further expected it will motivate individuals and teams to commit to and routinely implement the standards for composition and production of a balanced, tasty food supply with controlled salt content (2.5 g salt per luncheon serving [55]).

The coaching program was structured in five sessions, repeatedly following the Plan-Do-Check-Act cycle for a process of continual quality improvement (Fig. 1). Aside from short presentations to impart knowledge and report results of laboratory food analysis, moderated workshops were conducted to analyze the initial position, plan in a participatory process small, feasible, and potentially the most effective changes to salt-critical menu components, and evaluate their success or failure after implementation. In addition, catering team members completed short questionnaires to follow up on their awareness, attitudes, and motivation at different times, and to evaluate the overall program and the coaching (see below, measurements). In the final workshop, coach and catering team discussed benefits and gains in knowledge and skills, program success, and the prospect of sustainability within the particular organizational conditions. A formally trained member of the research group who is an experienced chef and registered dietician implemented the coaching program [56].

